### Study Population

A total of 150 patients with atopic dermatitis will be recruited at 3 sites: Geneva, Marburg, and Göttingen. The recruitment will be independent of the severity of disease and is limited to 50.0% (75/150) at each site. A sample size of 50 patients per group will have 84% power to detect a mean effect size of 0.6.

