### Methodology

We will randomize 150 patients diagnosed with atopic dermatitis 1:1:1 to arm 1 (irradiation for 30 minutes at 415 nm wavelength), arm 2 (irradiation for 30 minutes at 450 nm wavelength), and arm 3 (irradiation for 30 minutes at low-dose, placebo). We will stratify randomization by study site and initial EASI score (assessed during screening visit) with permuted and variable block sizes. For each strata combination, a list of separate randomization sequences will be generated using SAS 9.3 (Cary, NC). Irradiation will be scheduled 3 times a week for 8 weeks. Participants will be followed up for 4 weeks after the last irradiation. Patients will be blinded by wearing tinted protective goggles that disenable the distinction of different wavelengths of light. Medical doctors will examine patients in rooms other than those equipped with the investigational medical devices. These examiners are blinded and are, therefore, not involved in the preparation and process of irradiation. If the safety of an enrolled patient is potentially jeopardized, the investigator can break the blinding of the treatment. According to the predefined study schedule, we will measure skin pigmentation with a mexameter; take photos and blood samples; measure blood pressure; and gather data on Fitzpatrick skin type, DLQI, itch on visual analog scale, SCORAD, IGA, EASI, and PO-SCORAD scores. Detailed information on assessments is depicted in the study schedule (Multimedia Appendix 2). If the EASI score increases by 50% or more compared to baseline after at least 4 weeks of treatment (earliest: day 28=visit 13), a rescue scheme can be applied that allows the use of topical steroids or antihistamines. The investigator will decide whether to prescribe these medications, in what doses, and for how long. The respective patient will not drop out, but the rescue medication as well as the day of rescue will be documented. The study database will be provided by the Universitätsmedizin Göttingen, Ressort Forschung und Lehre, Referat Klinisches Studien Management using secuTrial, which is a browser-based electronic data capture system compliant with Good Clinical Practice (audit trail, role-rights concept). The database will be accessible via the internet.

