### Statistical Considerations

The primary analysis will be performed based on the full analysis set following the intention-to-treat principle. Dropouts during first 4 weeks of treatment will be replaced. Patients missing more than 5 irradiation appointments in total until day 25 (inclusive) or more than 3 consecutive irradiation appointments until day 25 (inclusive) will be considered dropouts and will be replaced. Dropouts after day 25 of the study protocol will not be replaced and will be analyzed in the intention-to-treat population. Sensitivity analysis will be done on the per-protocol population. The difference between the end of treatment after 8 weeks and baseline in primary effectiveness endpoint EASI will be analyzed using pairwise 2-sample *t* tests between each of both active treatments against placebo. As sensitivity analysis, an analysis of covariance will be used with study site, gender, and the hand out of topical emollient as additional factors and the EASI baseline value, age, and Fitzpatrick skin type as covariates. Other continuous secondary endpoints will be analyzed analogously. The EASI response will be analyzed primarily using chi-square test and as a sensitivity analysis with logistic regression. Time until treatment response will be analyzed using Kaplan-Meier estimator and log-rank test. In a further sensitivity analysis, if both wavelengths show better effectiveness than placebo, a pooled comparison against placebo will be done to increase the sample size.

The two comparisons, namely, 415 nm versus placebo and 450 nm versus placebo will be evaluated equally. To address the multiplicity, a success will be declared if both comparisons are statistically significant at an alpha level of .05 or if one of these two is statistically significant with respect to half of alpha at .025.

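### The pooled blue-light comparison is run only when both wavelengths already look better than placebo, so the estimate it reports is biased upward and its p-value is distorted given that it is run

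*Protocol article*

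**What the plan says.** All of this is in the protocol article. Under Methodology, allocation is 1:1:1 ("We will randomize 150 patients diagnosed with atopic dermatitis 1:1:1 to arm 1" and two further arms), so pooling the two wavelengths gives 100 against 50 patients. Under Study Population, the size is justified by a single comparison: "A sample size of 50 patients per group will have 84% power to detect a mean effect size of 0.6".

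Under Statistical Considerations, the primary analysis uses two-sample t "tests between each of both active treatments against placebo". The pooled comparison follows as an extra: "if both wavelengths show better effectiveness than placebo, a pooled comparison against placebo will be done to increase the sample size". Its status is set by the opening words of that sentence, "In a further sensitivity analysis". The section does not say whether *better* refers to direction or to significance.

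The success rule comes in the next paragraph and names only the two pairwise tests. One route needs both of them: "a success will be declared if both comparisons are statistically significant at an alpha level of .05". The alternative route needs only a single test, at a stricter level: "if one of these two is statistically significant with respect to half of alpha at .025". The pooled result has no place in it.

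**The concern.** The same EASI changes decide whether the pooled analysis is done and then supply its result. Trials in which chance made an active arm look poor are filtered out; trials in which chance flattered both arms, for instance through a poor placebo group, are kept. A reader sees the pooled figure only in the second kind, so its behaviour given that it was run is what applies to the published number.

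The estimate rests on 100 against 50 patients and has the smallest standard error of the blue-light contrasts, so it may be given more weight than a secondary analysis deserves. The condition also works against the stated purpose of gaining sample size: it withholds pooling when the pairwise results are mixed, which is when added precision would help most.

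**Working it through.** **Inputs.** 50 patients per arm and a planned effect of 0.6, read as a standardised difference (Study Population); 1:1:1 allocation (Methodology); alpha .05, or .025 for a single comparison (Statistical Considerations). Assumed, because the article does not state them: two-sided tests, normal data, equal SDs, and 50 analysed per arm without dropout. Effects are in SD units of the EASI change.

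**1. The plan's own figure.** Noncentrality = 0.6 × √(50/2) = 3.0. With 98 df and two-sided .05, the noncentral t distribution gives power 0.844 (normal approximation 0.851). The stated 84% is reproduced. Two-sided .025 gives 0.764 to 0.776 and one-sided .05 gives 0.909 to 0.912; neither reproduces it.

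**2. Structure of the pooled test.** Each pairwise difference has SE √(2/50) = 0.200. The two share the placebo arm, so their correlation is (1/50)/(2/50) = 0.5. The pooled difference is their mean, with SE √(1/100 + 1/50) = 0.173. Hence pooled z = (z₁ + z₂) × 0.100/0.173 = (z₁ + z₂)/√3.

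**3. Condition read as both numerically better, no true effect.**
- Chance that it is met: 1/4 + arcsin(0.5)/(2π) = 1/4 + 1/12 = 1/3.
- Mean of each z given that it is met: [(1 + 0.5)/(2√(2π))]/(1/3) = 0.299/0.333 = 0.898. Mean pooled estimate: 0.898 × 0.200 = 0.18 SD, about one standard error (0.18/0.173 = 1.04), where the truth is 0.
- Almost every favourable pooled rejection occurs with both arms ahead, so the rejection rate given that the test is run is 0.025/0.333 = 7.5%, all in favour of blue light, against a nominal 2.5% in that direction.

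**4. Condition read as both significant at .05.** The smallest possible pooled z is (1.96 + 1.96)/√3 = 2.26, above 1.96. The pooled result is settled before it is computed.

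**5. Simulation** (2,000,000 trials per scenario, three arms of 50, shared placebo, t tests). Each cell gives how often the condition is met, then the bias of the reported pooled estimate.

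| True effects, two active arms (SD) | Both numerically better | Success rule met and both better | Both significant at .05 |
|---|---|---|---|
| 0 / 0 | 33.3%; +0.179 | 2.2%; +0.388 | 0.5%; +0.484 |
| 0.3 / 0.3 | 88.5%; +0.036 | 35.3%; +0.173 | 17.1%; +0.244 |
| 0.6 / 0 | 50.0%; +0.120 | 44.4%; +0.142 | 2.5%; +0.349 |
| 0.6 / 0.3 | 93.3%; +0.021 | 75.6%; +0.067 | 30.5%; +0.176 |
| 0.6 / 0.6 (planned) | 99.7%; +0.001 | 89.8%; +0.033 | 74.9%; +0.068 |

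Under no effect, the pooled p-value is below .05 in 7.5%, 71.7% and 100.0% of the trials in which it is run (columns left to right). Counted over all trials, run or not, the chance of running it and finding p < .05 is 2.5%, 1.6% and 0.5%.

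**6. Without the condition.** Bias is 0.000 SD in every scenario, two-sided type I error is 0.050, and power at 0.6/0.6 is 93%.

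**The case against.** **Error control.** A reader might infer that the p-value is invalid outright, or that the trial's false-positive rate is inflated. The document does not support that. A condition of this kind can only remove rejections, as in ordinary hierarchical testing, and step 5 shows 0.5% to 2.5% over all trials. The distortion exists only given that the analysis is run. This objection stands in full.

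**A foregone conclusion.** A reader might also infer that the analysis can only confirm the primary result. That is true only if *better* means both significant. On the numerical reading, 92.5% of the null trials in which it is run are not significant. The numerical reading is arguably the more natural one, since the next paragraph of the same section speaks of statistical significance explicitly when that is meant. The full protocol or analysis plan, not shown, may define the word. The figures for the significance reading are therefore conditional on it, but bias is present under either definition.

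**Planned effect.** At 0.6 SD in both arms the bias is negligible on the numerical reading and about 11% of the effect (0.068/0.6) on the strictest. This also stands. The problem matters when one or both effects fall short of the plan.

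**Consequence.** The pooled result lies outside the success rule and cannot create a success. It is still a planned estimate that would be reported.

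**Reason for the condition.** The arms are different wavelengths, and averaging discordant results gives a number that describes neither. That is a fair caution, but showing the pairwise estimates alongside meets it without selecting on the outcome.

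**Conclusion.** The concern holds in a limited form. Given that the pooled analysis is run, its estimate is biased upward in every scenario computed and its p-value does not have its nominal distribution. On the numerical reading the bias runs from about 0.00 SD at the planned effects to 0.18 SD with no effect, and is 0.12 SD when only one wavelength works. On the both-significant reading it runs from 0.07 to 0.48 SD, and the test carries no evidence beyond the pairwise results.

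Neither the primary conclusion nor its error rate is affected, so this is a correctable weakness in a supportive analysis and no threat to the trial's main claim. The sizes rest on the assumptions listed with the inputs and on the undefined meaning of *better*; the direction of the bias is the same under all three meanings examined.

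**What to change.** Delete the condition. Suggested wording: *As a supportive analysis outside the success rule, the two blue-light arms combined will be compared with placebo whatever the pairwise results. The estimate and its 95% confidence interval will be shown next to the two pairwise estimates.*

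This is the same test on the same data, with no extra patients or assessments. There are two small costs. If the wavelengths differ in effect, the pooled figure is an average that fits neither, which is why the pairwise estimates must stand beside it. And the article's Results section reports that enrolment is complete and analysis has begun, so the change has to be documented and dated before unblinded results are used. If that is no longer possible, report the pooled comparison anyway, state the condition and when it was dropped, and call the result descriptive.

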Other smaller studies investigated the effect of blue light on patients with psoriasis. Pfaff et al [12] used a localized blue light device (wavelength: 453 nm) to treat 49 patients with mild psoriasis for 30 minutes daily or almost daily for 12 weeks with 4 weeks of follow-up. After 78-90 days, the Local Psoriasis Severity Index significantly decreased compared to an untreated area (mean 0.92 [SD 1.10]). No treatment-related AEs occurred. Weinstabl et al [13] reported on localized irradiation of 40 patients with mild to moderate psoriasis with blue light. Group 1 (n=20) received treatment at home with blue light (LED, emission maximum: 420 nm) for 15 minutes once daily for 4 weeks (2 weeks follow-up). Group 2 (n=20) received treatment with another blue light device (LED emission maximum: 453 nm). The contralateral control plaques remained untreated in both groups. In both groups, the Local Psoriasis Severity Index significantly decreased in treated areas compared with that in untreated areas. No severe AEs occurred. Slight transient hyperpigmentation was noted after 3 weeks in both groups (59% and 50%, respectively). However, an FBB light device has not been clinically tested outside the mentioned studies.

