The two risk differences between one of each blue light irradiation treatments against placebo of the rates of patients with at least one device-related adverse event (rated as possible, probable, or certain) will be compared using asymptotic Wald test of noninferiority for the risk difference. Missing values for the primary and secondary endpoints will be replaced using proper single regression methods (IVEware; University of Michigan, Ann Arbor, MI). Besides the scores (such as EASI scores), the study site, study visits with the documented EASI score, treatment group, gender, age, hand out of topical emollient, and Fitzpatrick skin type will be included in the regression models. In safety analysis, per-protocol analysis, and explorative analysis, missing values will not be replaced.

After the completion of the treatment phase of about 75 patients, first, the EASI score difference between the end of treatment and baseline and, second, the rates of device-related AEs will be analyzed descriptively using *t* test and Fisher’s exact test, as appropriate (interim analysis). Based on the estimates, it will be evaluated whether a total of 150 patients will be sufficient to show superiority against placebo at the end of the study.

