### Safety and Risk to Benefit Rationale

Foreseeable AEs include thermal discomfort during the irradiation and increased skin pigmentation, which we expect to be of a very mild nature as experienced in previous trials. Due to the absence of UV light in our devices, we do not expect dermatitis solaris (sunburn) or an increased risk for melanoma or nonmelanoma skin cancer.

Unexpected physical accidents during the irradiation procedure itself (eg, the patient falling off the examination bed or a deficient device harming participants’ physical integrity) are possible out of general considerations. The non-CE mark investigational medical devices are classified as Class IIa according to Annex IX of the Directive 93/42/EEC and as Risk Group 2 devices according to EN 60601-2-57. They have been approved by competent federal authorities (BfArM, Suisse Medic). Precautions have been taken by means of risk management, testing, and protocol design to protect the health and safety of the patients and personnel participating in the clinical study. All AEs will be recorded and documented. Serious AEs will be reported in accordance with the appropriate legal regulations (Medizinprodukte-Sicherheitsplanverordnung). Due to the well-documented efficacy of blue light treatment in psoriasis and eczema, clinical benefits include an improvement in objective disease severity and quality of life (less itching or less insomnia expected).

In summary, blue light has the potential to improve inflammatory skin diseases. Associated risks are rare, mild, and transitory. After re-evaluation of the risks, the overall residual risk has been concluded to be satisfactory. As an overall result, we conclude that the benefits for the patients outweigh residual risk, thereby justifying the introduction of the device.

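### The Wald noninferiority test for device-related adverse events, at about 50 patients per arm, exceeds its nominal level if placebo events are rare; a score-based test avoids this

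*Protocol article*

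**What the plan says.** In the protocol article, Statistical Considerations says of the formal safety comparison, made once for each active arm against placebo, that the rates "will be compared using asymptotic Wald test of noninferiority for the risk difference". The endpoint is the proportion of patients with "at least one device-related adverse event (rated as possible, probable, or certain"). Missing values are not replaced in the safety analysis.

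The arm size comes from Methodology ("We will randomize 150 patients diagnosed with atopic dermatitis 1:1:1") and from Study Population ("A sample size of 50 patients per group will have 84% power to detect a mean effect size of 0.6"). That power statement concerns efficacy. The two-part alpha rule in Statistical Considerations (success "if both comparisons are statistically significant at an alpha level of .05", or if one is significant at .025) is also set out for the efficacy comparisons.

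For the safety test the article gives no margin, no alpha and no expected event rate. A journal article may leave these to the full protocol or analysis plan, and their absence is not criticised here. The choice of test is in the text, and the point concerns that choice.

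**The concern.** The Wald test estimates its variance from the observed proportions. When one or both are near zero, that variance is too small, the upper confidence limit sits too low, and noninferiority is declared too often. The error favours calling the device safe, in the formal safety comparison of a device that is not CE-marked.

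The article gives some reason to expect few placebo events. Under Investigational Devices, the placebo output is 0.2 mW/cm² against 40 mW/cm² in the active arms (40 / 0.2 = 200-fold lower), and the placebo module has no fans. The Safety and Risk to Benefit Rationale says: "Associated risks are rare, mild, and transitory".

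**Working it through.** **The plan's own figure.** With 50 per group and effect size 0.6, the noncentrality is 0.6 × √(50/2) = 3.0. At two-sided .05 the normal approximation gives Φ(3.0 − 1.96) = 85.1%, and the noncentral t with 98 df gives 84.4%. The stated 84% is reproduced, so 50 per arm is the size set for efficacy.

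**Inputs for the safety test.** From the article: n = 50 per arm, Wald test on the risk difference. Assumed: one-sided alpha 2.5%, margin m of 5 to 20 points, placebo rate p0 of 0 to 30%.

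**Formulas.** With x1 and x0 events (active, placebo) and observed rates q1 = x1/50 and q0 = x0/50:

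- Wald: declare noninferiority if q1 − q0 + 1.96 × √{[q1(1 − q1) + q0(1 − q0)]/50} < m.
- Score (Farrington-Manning): declare it if (q1 − q0 − m)/SE < −1.96, where SE uses the maximum-likelihood rates under the restriction p1 − p0 = m.
- Type I error: the sum of Bin(x1; 50, p0 + m) × Bin(x0; 50, p0) over all of the 51 × 51 outcomes that lead to a declaration.

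**One cell by hand: p0 = 0, m = 10 points.** Placebo events are then always 0.

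- x1 = 2: Wald limit 0.04 + 1.96 × √(0.04 × 0.96/50) = 0.094, below 0.10, so noninferiority is declared.
- x1 = 3: Wald limit 0.126, so it is not.
- Wald type I error = P(X ≤ 2 | 50, 0.10) = 0.0052 + 0.0286 + 0.0779 = 11.2%.
- Score test at x1 = 2: (0.04 − 0.10)/√(0.10 × 0.90/50) = −1.41, so noninferiority is not declared. Only x1 = 0 passes, giving 0.90^50 = 0.5%.

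**All cells: exact type I error in %, Wald / score, nominal 2.5%.**

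| Placebo rate | m = 5 | m = 7.5 | m = 10 | m = 15 | m = 20 |
|---|---|---|---|---|---|
| 0% | 7.7 / 0.0 | 10.3 / 2.0 | 11.2 / 0.5 | 4.6 / 1.4 | 4.8 / 1.8 |
| 1% | 5.8 / 0.4 | 6.8 / 1.7 | 7.8 / 1.5 | 5.2 / 1.9 | 5.2 / 2.1 |
| 2% | 5.4 / 0.9 | 5.0 / 1.8 | 5.8 / 2.1 | 5.0 / 1.9 | 4.9 / 2.1 |
| 5% | 3.6 / 2.0 | 3.4 / 2.0 | 3.7 / 2.2 | 3.8 / 2.2 | 3.8 / 2.2 |
| 10% | 2.9 / 2.4 | 2.9 / 2.3 | 3.0 / 2.3 | 2.8 / 2.5 | 3.1 / 2.5 |
| 20% | 2.7 / 2.6 | 2.7 / 2.6 | 2.8 / 2.6 | 2.7 / 2.5 | 2.5 / 2.7 |
| 30% | 2.7 / 2.7 | 2.7 / 2.7 | 2.6 / 2.6 | 2.5 / 2.6 | 2.5 / 2.5 |

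At nominal one-sided 5% the pattern is the same: Wald gives 7.7-11.2% at a placebo rate of 0%, 7.0-9.4% at 2%, and 4.9-5.4% at 20-30%.

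**No events in either arm.** The Wald standard error is 0, so the upper limit is 0 and lies below any positive margin (strictly, the z statistic has a zero denominator). For the score test the restricted rates are m and 0, and solving m/√[m(1 − m)/50] = 1.96 gives m = 1.96²/(50 + 1.96²) = 3.84/53.84 = 7.1%. The two tests therefore disagree at 0/50 against 0/50 only for margins below about 7 points (5.1 points at one-sided 5%). With a placebo rate of 0%, the chance of no events in both arms is 0.98^50 = 36% if the active rate is 2%, 0.95^50 = 7.7% if it is 5%, and 0.5% if it is 10%.

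**The case against.** The strongest objection is that the premise is not in the document. No expected placebo rate is stated. The endpoint counts anything rated at least possibly related, over 24 sessions (3 a week for 8 weeks), and examiners are blinded. The earlier full-body study reported redness, warmth and itching, and redness and itch are also features of atopic dermatitis. Placebo patients could therefore collect events rated as possible, and at a placebo rate of 10% or more the table shows almost no problem. This stands: a reader might infer that the test will be anticonservative, but the article supports only that it is so if placebo events are rare. The 11.2% is the worst cell and depends on an assumed margin.

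A reader might also infer that zero events would wrongly deliver noninferiority whatever the margin. They would not: above about 7 points the score test reaches the same conclusion.

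A third tempting reading concerns pigmentation. The article cites a psoriasis study in which "Slight transient hyperpigmentation was noted after 3 weeks in both groups (59% and 50%, respectively"), and lists increased pigmentation as foreseeable. One might conclude that the endpoint is bound to fail and that pigmentation should be taken out. The document does not support this. Those figures come from localized psoriasis treatment. If the true rates differed that much, failing to show noninferiority would be the correct result, and removing a foreseeable event would make the safety claim easier. The Endpoints section already makes change in hyperpigmentation a separate safety endpoint. Calling the risks rare beside those figures is loose wording, with no bearing on the test.

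**Conclusion.** The point holds conditionally. At 50 per arm, one-sided 2.5% and margins of 5 to 20 points, the Wald test runs at about 1.8 to 4.5 times its nominal level (4.6/2.5 to 11.2/2.5) if the placebo rate is 0-2%. The excess is modest at 5%, and the test is close to nominal from 10% upwards. The score test stays at or below 2.1% for placebo rates of 0-2% and between 2.0% and 2.7% for rates of 5-30%.

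The margin, alpha and placebo rate are all assumptions. A low placebo rate is plausible from the device settings and the risk summary, but it is not stated. Since the score test protects the level where Wald fails and gives up little level control elsewhere, the change is worth making without knowing the rate. It concerns the safety comparison only; the primary efficacy analysis is untouched.

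**What to change.** In Statistical Considerations, replace the asymptotic Wald test with a score-based noninferiority test and the matching confidence interval (Farrington-Manning or Miettinen-Nurminen) for both active-against-placebo comparisons. Keep the endpoint as defined, and continue to report hyperpigmentation separately as the Endpoints section plans.

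In programming terms this is one procedure option and a sentence. The statistical cost is larger when events are rare. Summing the same outcome probabilities at p1 = p0 instead of p0 + m gives the chance of showing noninferiority:

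- Equal true rates of 2%, 10-point margin: it falls from about 93% (Wald) to about 65% (Farrington-Manning) or 62% (Miettinen-Nurminen).
- Equal true rates of 2%, 5-point margin: it falls from about 46% to about 10%.

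Much of that loss is the removal of the Wald test's excess error, though the score test is itself conservative in some of these cells. At placebo rates of 10% or more the type I errors of the two tests differ by less than one percentage point. The chance of showing noninferiority differs by up to about 7 points at a rate of 10% and by no more than about 3 points at 20%.

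### Missing endpoints are imputed once and then tested as if observed, so standard errors are too small and the stated alpha is exceeded by an amount that depends on late dropout

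*Protocol article*

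**What the plan says.** All of this is in the protocol article, mostly under Statistical Considerations.

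- **Missing data.** "Missing values for the primary and secondary endpoints will be replaced using proper single regression methods". Besides the scores, the imputation models include "the study site, study visits with the documented EASI score, treatment group, gender, age, hand out of topical emollient, and Fitzpatrick skin type". Safety, per-protocol and explorative analyses are left unimputed.
- **Analysis set.** "The primary analysis will be performed based on the full analysis set following the intention-to-treat principle". Dropouts up to day 25 are replaced by new patients. For later ones: "Dropouts after day 25 of the study protocol will not be replaced and will be analyzed in the intention-to-treat population".
- **Primary test.** The EASI change from baseline to week 8 "will be analyzed using pairwise 2-sample *t* tests between each of both active treatments against placebo".
- **Success rule.** "a success will be declared if both comparisons are statistically significant at an alpha level of .05", or if one of them is significant at .025.
- **Size.** Under Study Population: "A sample size of 50 patients per group will have 84% power to detect a mean effect size of 0.6". Allocation is 1:1:1 (Methodology).

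The text mentions neither multiple imputation nor any pooling rule or other variance correction.

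**The concern.** The word *proper* describes how a missing value is drawn: the regression coefficients and the residual are both sampled, so the value carries the right uncertainty. That uncertainty reaches the standard error only if the draw is repeated and the spread between completed data sets is added to the variance. With one completed data set there is no such spread to measure. The t test divides by the full 50 per arm and treats each imputed value as a patient who was seen at week 8.

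Three things follow: confidence intervals are too narrow, the .05 and .025 thresholds no longer deliver the error rates they name, and the result depends on one random draw. The error always runs towards declaring success. The analysis of covariance planned as a sensitivity analysis is not exempted from imputation, so it would use the same filled-in data.

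**Working it through.** **Inputs from the article.** 50 per arm, three arms, t test on EASI change at week 8, success if both p < .05 or one p < .025, standardised effect 0.6, power 84%. Sidedness is not stated.

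**Assumed, because the article does not give them.** The missing fraction p at week 8 (5-30%), the correlations between visits, normal outcomes, and data missing at random or completely at random.

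**Step 1: reproduce the stated power.** The noncentrality is 0.6 × √(50/2) = 3.0. The normal approximation with two-sided .05 is Φ(3.0 − 1.96) = 85.1%. The exact noncentral t with 98 degrees of freedom gives 84.4%, which matches the stated 84%. At .025 the exact figure is 76.4%. So two-sided .05 per comparison is used below.

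**Step 2: large-sample formula for the understatement.** Let k be the variance of week-8 EASI left unexplained by the imputation predictors, divided by the variance of the change. The t test reports a variance of σ²/n per arm. The true variance after one proper draw is

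(σ²/n) × [1 + k × 2p/(1 − p)].

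Half of the added term comes from the lost observations. The other half is noise from the single draw.

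Assume equal variances (set to 1), correlations of 0.5 (baseline to week 8) and 0.7 (week 4 to week 8), and 0.5 between baseline and week 4.

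- R² of week 8 on both predictors = (0.25 + 0.49 − 2 × 0.5 × 0.7 × 0.5)/(1 − 0.25) = 0.39/0.75 = 0.52.
- The residual variance is 0.48, the variance of the change is 2 × (1 − 0.5) = 1, so k = 0.48.
- At p = 10%: 1 + 0.48 × 0.2/0.9 = 1.107. The true SD divided by the reported SE is √1.107 = 1.052. The error is 2 × [1 − Φ(1.96/1.052)] = 6.2%.
- At 5, 20 and 30% the same steps give SD/SE ratios of 1.025, 1.114 and 1.188, and errors of 5.6, 7.8 and 9.9%.

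**Step 3: simulation under no true effect, same correlations.** Ranges are over separate runs; Monte Carlo error is about 0.2-0.3 points.

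| Week-8 EASI missing | Error per comparison, nominal 5% | Familywise error, trial's rule |
|---|---|---|
| 5% | 5.6-6.0% | 5.4-5.8% |
| 10% | 6.3-6.5% | 5.9-6.3% |
| 20% | 8.2-8.6% | 7.9-9.0% |
| 30% | 9.7-10.4% | 10.6-11.0% |

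With complete data the familywise figure in these runs is 5.1-5.3%.

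**Step 4: dependence on how well the predictors work.** In 40,000 trials per cell, with ρ the assumed correlation of the imputation predictors with the outcome, error per comparison at nominal 5% was:

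| Missing | ρ = 0.8 | ρ = 0.5 | ρ = 0 |
|---|---|---|---|
| 6% | 5.5% | 6.1% | 6.6% |
| 10% | 5.8% | 6.8% | 7.5% |
| 20% | 7.2% | 9.4% | 11.0% |
| 30% | 8.9% | 12.6% | 15.1% |

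The formula agrees. For ρ = 0.5, k = 1 − 0.25 = 0.75. At 20% missing, √(1 + 0.75 × 0.4/0.8) = 1.173, against a simulated SD/SE ratio of 1.169.

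In another run, one later visit correlated 0.85 with week 8 was added to the Step 3 predictors. Familywise error was then 5.2, 5.6 and 6.7% at 5, 10 and 20% missing.

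**Step 5: the remedy.** Multiple imputation from the same model (20 data sets, Rubin's rules) gave 4.8-5.1% per comparison and 4.5-4.8% familywise in all twelve cells of Step 4.

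**The case against.** **Little may need imputing.** Patients lost up to day 25, including those who miss too many sessions, are replaced. The imputed week-8 values then belong mainly to losses between day 25 and week 8. This stands as a limit on size: near 5% missing the excess is under one percentage point familywise. It does not remove the defect, because the plan sets no ceiling on late loss.

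**The stated imputation model is richer than the simulated one.** It includes other scores and all visits with a documented EASI score, and a patient lost late may have visits close to week 8. This also stands. Step 4 shows that the inflation shrinks but persists. The assessment schedule is in an appendix that is not shown, so any correlation is an assumption.

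**The per-protocol analysis is not imputed.** A gross artefact might show up there. But it covers a different population and does not correct the primary test.

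**The SAP may settle it.** The article names single imputation explicitly, so this is a stated method and not a detail left open. An SAP with multiple imputation would contradict the article.

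**Stronger readings that the documents do not support.**

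- A reader might infer that the false-positive rate is doubled. That needs about 30% late missingness under the main assumptions, and nothing in the article supports such a rate.
- A reader might infer from the named software that multiple imputation is intended or comes at no cost. The article gives only the program's name and origin, and the method it states is single.
- A reader might want the documented rescue medication added to the imputation model. That is unrelated to single versus multiple imputation, and the calculations here do not bear on it.

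**Conclusion.** The point holds in conditional form. Followed as written, the plan understates the standard error of both primary comparisons whenever week-8 EASI is missing, and the stated alpha is exceeded. Under the assumed correlations of 0.5 and 0.7, familywise error is about 5.5% with 5% missing, 6% with 10%, 8-9% with 20% and 11% with 30%. The direction does not depend on these assumptions; the size does. The multiplicity rule is not at fault, since with complete data it stays close to 5%. This should be fixed, but the documents do not show that the trial's conclusion would be seriously distorted. That would require substantial late dropout, for which they give no figure.

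**What to change.** Keep the imputation model as listed. Create at least 20-50 imputed data sets, run each primary and secondary endpoint analysis on every one, and combine estimates and standard errors by Rubin's rules with small-sample degrees of freedom. A likelihood-based repeated-measures model on the observed visits is an equally valid alternative. Correct the word *single* in the text to match.

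**Timing.** The Results section says that enrolment is complete and analysis is under way, so this changes a prespecified primary analysis. Document it before unblinding. If that is no longer possible, report the pooled analysis as a labelled sensitivity analysis beside the prespecified result.

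**Cost.** Trial conduct does not change. Confidence intervals become slightly wider: with many imputations the factor is about √(1 + k × p/(1 − p)). For k = 0.48 this is √(1 + 0.48 × 0.1/0.9) = 1.026 at 10% missing and √(1 + 0.48 × 0.2/0.8) = 1.058 at 20%. Power for an effect of 0.6 (ρ = 0.5, per comparison at .05) was 81.3% with 10% missing and 76.7% with 20%, against 84.3% with complete data. Single imputation appeared to give 82.8% and 80.8%, but at an inflated error rate.
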